## Abstract

**Background:**

Effective interventions, targeting key contributory causal factors, are needed to prevent the emergence of severe mental health problems in young people. Insomnia is a common clinical issue that is problematic in its own right but that also leads to the development and persistence of psychotic experiences. The implication is that treating sleep problems may prevent the onset of psychosis. We collected initial case series data with 12 young people at ultra-high-risk of psychosis. Post-intervention, there were improvements in sleep, depression and psychotic experiences. Now we test the feasibility of a randomised controlled trial, with a clinical aim to treat sleep problems and hence reduce depression, psychotic experiences, and prevent transition to psychosis.

**Methods and analysis:**

A randomised controlled feasibility trial will be conducted. Forty patients aged 14 to 25 years who are at ultra-high-risk of psychosis and have sleep disturbance will be recruited from National Health Service (NHS) mental health services. Participants will be randomised to receive either a novel, targeted, youth-focussed sleep intervention in addition to usual care or usual care alone. Assessor-blinded assessments will be conducted at baseline, 3 months (post-intervention) and 9 months (follow-up). The eight-session psychological intervention will target the key mechanisms which disrupt sleep: circadian rhythm irregularities, low sleep pressure, and hyperarousal. To gain an in-depth understanding of participants’ views on the acceptability of the intervention and study procedures, 16 participants (n=10 intervention, n=6 control) will take part in qualitative interviews. Analyses will focus on feasibility outcomes (recruitment, retention, and treatment uptake rates) and provide initial CI estimates of intervention effects. Thematic analysis of the qualitative interviews will assess the acceptability of the intervention and trial procedures.

**Ethics and dissemination:**

The trial has received ethical approval from the NHS Health Research Authority. Findings will be disseminated through peer-reviewed publications, conference presentations, and lay networks.

**Trial registration number:**

ISRCTN85601537.

Strengths and limitations of this study*Importance of the study:* The SleepWell trial is the first randomised controlled test of a sleep intervention in young patients at ultra-high-risk of psychosis.*Causal-interventionist paradigm:* This is the first randomised controlled trial to target a single causal factor in the ultra-high-risk group: the randomised controlled design has the aim of lessening sleep disturbance in the intervention group, thereby testing the underlying theory that sleep disruption is a contributory causal factor in the occurrence of psychotic experiences (most likely via reductions in negative affect).*Data collection methods:* The study uses mixed methods (interviews, questionnaires and wearable technology) to address the research questions.*Follow-up period:* The follow-up period is 9 months; however, the risk of onset of psychosis may be elevated for longer, meaning that we cannot capture all information about transition rates.*Control condition:* There is no active control, so it is not possible to determine which elements of the intervention may produce change.*Importance of the study:* The SleepWell trial is the first randomised controlled test of a sleep intervention in young patients at ultra-high-risk of psychosis.*Causal-interventionist paradigm:* This is the first randomised controlled trial to target a single causal factor in the ultra-high-risk group: the randomised controlled design has the aim of lessening sleep disturbance in the intervention group, thereby testing the underlying theory that sleep disruption is a contributory causal factor in the occurrence of psychotic experiences (most likely via reductions in negative affect).*Data collection methods:* The study uses mixed methods (interviews, questionnaires and wearable technology) to address the research questions.*Follow-up period:* The follow-up period is 9 months; however, the risk of onset of psychosis may be elevated for longer, meaning that we cannot capture all information about transition rates.*Control condition:* There is no active control, so it is not possible to determine which elements of the intervention may produce change.

## Background

### Rationale

The peak age of onset for mental health problems, including psychosis, is between the ages of 14 and 25 years. Three quarters of all lifetime instances of mental health disorders have started by the age of 24.^1^ There is increasing recognition of the need to develop preventative approaches.^2^ We focus on psychosis, with an emphasis on developing interventions that result in both immediate and longer-term improvements by individually targeting developmentally important, transdiagnostic causal factors, that are problematic in their own right and that young patients want treated. Sleep disturbance is one such issue.

In young people, sleep disruption is associated with poor physical and mental health and worse social outcomes, including greater suicide risk, obesity, and lower educational attainment.^3 4^ Yet, sleep problems have been historically understood as either a symptom of psychiatric disorder or a non-specific epiphenomenon (ie, a secondary problem). Recent research has turned this traditional view on its head and instead shown that sleep disruption is one causal factor in the occurrence of psychotic experiences.^5 6^

When sleep is deliberately reduced, in experimental manipulation studies, it results in an increase in psychotic experiences.^7^ Increases in psychotic experiences due to worsening of sleep are mediated by increases in negative affect and related processes (such as worry and negative self-views).^7^ Conversely, successfully treating sleep problems leads to an improvement in psychotic experiences. A large randomised controlled trial (RCT) with 3755 university students found that psychological treatment was highly effective for treating insomnia and led to significant improvements in non-clinical hallucinations and paranoia.^8^ Sleep treatment in this trial also reduced the likelihood that students would reach the threshold for being at ultra-high-risk of psychosis.

In young people at ultra-high-risk of psychosis, sleep problems are widespread, with estimates of prevalence exceeding 75%.^9^ Insomnia and circadian rhythm disruption are associated with the severity of psychotic experiences and poor outcomes.^10–13^ Findings from a large European prospective multicentre study indicate that sleep problems are highly predictive of transition to psychosis.^14^ In addition, sleep disturbance is also a contributory factor across a wide range of other mental health problems, including anxiety, depression, and bipolar disorder.^6 15^ Therefore, treating sleep problems may also prevent other mental health problems, such as depression and anxiety, and promote improvements in functioning and physical health.

The key diagnostic marker for identifying young people at ultra-high-risk of psychosis is the presence of attenuated (subthreshold frequency or intensity) psychotic experiences (APE). Yet APE are a marker of potential risk for a number of different serious mental health problems, including personality and mood disorders.^16^ Even for young people who experience APE but do not go on to meet diagnostic criteria for psychosis (or other serious mental health problems) the long-term outcomes can remain poor.^17 18^ The clinical staging model in psychiatry emphasises that less differentiated early phases of mental health problems may benefit from broad spectrum and simpler treatments.^19–21^ From a network perspective, mental health problems arise from the causal interplay (both direct and reciprocal) between different symptoms.^22^ Therefore, targeting one specific symptom, such as sleep disturbance, will have an impact on other causally connected problems, such as low mood, anxiety, and psychotic experiences.

Cognitive Behavioural Therapy for insomnia (CBTi) is the first-line treatment for adults with insomnia^23 24^ and has been effectively adapted for people with psychosis.^5 25 26^ Not only does CBTi lead to large improvements in insomnia, but there are also significant effects on depression and anxiety,^8 25 27^ and smaller effects on psychotic experiences.^8 25^ It is likely the treatment effects on psychotic experiences are mediated by improvements in depression and anxiety.^8 27^ In light of this previous work, we now want to test the effects of treating sleep problems to reduce psychotic experiences and prevent the onset of psychosis in those at highest risk. We are also interested in whether this treatment focus reduces emotional disorders both in the short and long-term.

Building on the principles of CBTi and our work treating insomnia in adults with psychosis, we developed a brief psychological intervention to address sleep problems in young people at ultra-high-risk of psychosis (SleepWell).^28^ The core treatment techniques include stimulus control, circadian realignment, and regulating daytime activity. In an uncontrolled case series with 12 young people at ultra-high-risk of psychosis, outcome assessments were conducted pre-treatment, post-treatment, and at a 1-month follow-up. Following the intervention, there were improvements in sleep (*d*=6.8), depression (*d*=0.5), and psychotic experiences (paranoia *d*=0.6 and hallucinations *d*=0.3) and the changes were maintained at the 1-month follow-up. Throughout the 10-week study period, no participants transitioned to psychosis. In the opposite direction, at the end of the study three participants no longer met criteria for being at ultra-high-risk of psychosis. The treatment was popular (for example, 89% attendance rate) and patients were keen to participate. In qualitative interviews, participants described achieving meaningful change in both sleep and well-being by developing a ‘repertoire of skills’.^29^ The treatment now requires testing in a randomised trial to determine the effects on psychotic experiences and the potential to prevent the onset of psychosis.

Due to limitations in statistical power, we will investigate the effects of the sleep treatment on the dimension of psychotic experiences rather than relying solely on the dichotomous outcome of transition. In line with the findings from all previous studies, we expect that the effect of improving sleep on psychotic experiences will be through improvements in negative affect (depression and anxiety), which is a mediator we are also interested in as an outcome in itself.

### Objectives

We aim to assess the feasibility of a targeted intervention to improve sleep and prevent psychosis in young people at ultra-high-risk of psychosis.

The primary objective is to assess the feasibility and acceptability of a targeted sleep intervention to prevent psychosis in young people at ultra-high-risk in order to establish the key parameters for a definitive RCT. The secondary research objective is to gather data on clinical outcomes to provide a preliminary indication of the clinical efficacy of the sleep intervention (SleepWell) for young people attending National Health Service (NHS) mental health services with sleep problems who are at ultra-high-risk of psychosis. Table 1 provides a summary of the objectives (and the associated feasibility markers or assessment measures).

**Table 1 T1:** Summary of objectives and assessment measures

	Objectives	Outcome measures
Primary	Assess the feasibility and acceptability of a targeted sleep intervention to prevent psychosis and to establish key parameters for a future randomised controlled trial.	Number of patients identified, recruited, declined and retained.
		Number of referrals made per site, and per service type, per month.
		Service use as measured on the CSRI.
		Completion rate of each assessment measure, including wearable-technology devices. Time taken to complete each assessment.
		Location and attendance at treatment sessions; content covered in treatment sessions; feedback from qualitative interviews; treatment acceptability score (AARP).
		Service use data completeness, time taken to collect service use data.
Secondary	Gather data on clinical outcomes to provide a preliminary indication of the clinical effectiveness of a novel sleep intervention (SleepWell) in addition to usual care versus usual care alone in young people with sleep problems who are at ultra-high-risk of psychosis attending NHS mental health services	Sleep disturbance: ISI; Sleep-50 CRD; Sleep diary; Actigraphy; Fatigue. Attenuated psychotic experiences: CAARMS; SPEQ-H; R-GPTS; ČEFSA. Psychiatric symptoms: DASS-21; C-SSRS; DWQ; BCSS. Activity and social functioning: Time budget; WASA; Oxford Agoraphobic Avoidance Scale; actigraphy. Physical health: BMI; step-count; BESAA; PHQ15; MAP. Quality of life: QPR; ReQoL; EQ5D. Service use: CSRI; and medication. Participant ranking of clinical outcome variables.
Qualitative	To explore the acceptability of study procedures to service users.	Feedback from qualitative interviews.

AARP, Abbreviated Acceptabliity Rating Profile; BCSS, Brief Core Schema Scale; BESAA, Body Esteem Scale for Adults and Adolescents; CAARMS, Comprehensive Assessment of At-Risk-Mental States; CRD, Circadian Rhythm Disruption; CSRI, Client Service Receipt Inventory; C-SSRS, Columbia Suicide Severity Rating Scale; DASS-21, Depression, Anxiety, and Stress Scale; DWQ, Dunn Worry Questionnaire; ČEFSA, Černis Felt Sense of Anomaly Scale; ISI, Insomnia Severity Index; MAP, Maudsley Addiction Profile; NHS, National Health Service; PHQ15, Patient Health Questionnaire; QPR, Process of Recovery Questionniare; R-GPTS, Revised Green et al Paranoid Thoughts Scale; SPEQ-H, Specific Psychotic Experiences Questionnaire - Hallucinations subscale; WASA, Work and Social Adjustment Scale.

Our hypotheses related to clinical outcomes are:

Compared with usual care, the SleepWell therapy added to usual care will reduce insomnia and other sleep disruption (post-treatment).Compared with usual care, the SleepWell therapy added to usual care will reduce psychotic experiences (a key marker of psychosis risk) and rates of transition to psychosis (post-treatment).Compared with usual care, the SleepWell therapy added to usual care will reduce psychiatric symptoms (depression, anxiety, worry, suicidal ideation), increase activity and social functioning, improve physical health, and enhance quality of life (post-treatment).Treatment effects will be maintained at follow-up.

## Methods and analysis

### Trial design and flow chart

The design is a prospective, parallel group, single blind, randomised controlled feasibility trial to evaluate a novel sleep intervention (SleepWell) in addition to usual care versus usual care alone in young people with sleep problems who are at ultra-high-risk of psychosis and attending NHS mental health services. Standard care will be measured, but remain as usual in both groups. Assessments will be carried out at 0 (baseline), 3 (post-treatment) and 9 (follow-up) months by a researcher blind to treatment allocation. An embedded qualitative study will explore the acceptability of study procedures to participants. A summary of the trial design can be seen in figure 1. The trial is prospectively registered with the ISRCTN registry: ISRCTN85601537. There is a trial Data Monitoring and Ethics Committee (DMEC) and Lived Experience Advisory Panel (LEAP). The LEAP is facilitated by the McPin Foundation.

**Figure 1 F1:**
[figure not shown]
Trial flow diagram.

### Randomisation, blinding and code-breaking

Participants will be randomised once they have completed the baseline assessment. Participants will be allocated to one of the trial arms using a 1:1 allocation ratio. Randomisation will be carried out by a validated online system, Sortition, designed by the University of Oxford Primary Care Clinical Trials Unit. Allocation will be carried out using a non-deterministic minimisation algorithm to ensure balance across groups with respect to severity of sleep disturbance (Insomnia Severity Index (ISI) score ≤21/≥22) and referring service (early intervention in psychosis team (EIP), child and adolescent mental health services (CAMHS), improving access to talking therapies service (IAPT)).

The research assessor will be blinded to group allocation, but the patients and clinician delivering the intervention will not be (they cannot be blinded to whether a psychological intervention is delivered or received). If an allocation is revealed between assessment sessions, this is logged by the trial coordinator and future assessments conducted, where possible, by another assessor to re-establish the blind.

### Participants

The trial participants will be 40 young people (aged 14 to 25 years) attending NHS mental health services with sleep problems who are at ultra-high-risk of psychosis. The principal method of recruitment will be via seeking referrals from the relevant clinical teams in the participating NHS mental health trusts. The services include specialist early intervention in psychosis services (EIP: ages over 14 years), child and adolescent mental health services (CAMHS: ages 0 to 18 years) and improving access to psychological therapies services (IAPT: ages over 18 years). The study will be advertised within participating NHS trusts and on social media so that young people receiving care in the recruiting NHS trusts can self-initiate referral to the trial. With the approval of the clinical team, all young people interested in taking part will then be approached by the research team, given information about the trial, and the screening conducted. The importance of self-initiated referral was highlighted by our LEAP to ensure accessibility and inclusivity. Informed consent will be obtained from all patients before participation.

#### Inclusion criteria

Aged 14 to 25 years;Patient of mental health services (at the time of referral to the study);Meet diagnostic criteria for ultra-high-risk of psychosis on the Comprehensive Assessment of At-Risk-Mental-States (CAARMS);^30^Experiencing current sleep problems (defined as a score >15 on the Insomnia Severity Index (ISI)^31^);Would like help to improve sleep; andWilling and able to give informed consent (or assent with parent/guardian consent for participants aged 14 to 15 years) for participation in the trial.

#### Exclusion criteria

Diagnosis of a primary severe mental health problem (including psychosis, bipolar disorder, personality disorder);Likely primary diagnosis of sleep apnoea (established using the STOP-BANG screen^32^);A primary diagnosis of alcohol or substance disorder;Organic syndrome;Significant learning disability; orCurrent engagement in any other individual psychological therapy.

### Assessments

Basic demographic and clinical data will be collected (eg, age, gender, ethnicity, clinical diagnosis). Clinical outcomes including sleep disturbance, psychotic and affective symptoms, social functioning, quality of life and physical health will be assessed at all three time points (baseline 0 months, post-intervention 3 months and follow-up 9 months).

Insomnia (ISI),^31^ circadian rhythm disruption (SLEEP-50 CRD subscale^33^) and fatigue^34^ will be assessed via self-report. Sleep and activity levels will also be assessed using actigraphy (over 7 days), complemented with sleep diaries and a time-budget assessing meaningful activity.^35^

Attenuated psychotic symptoms and transition to psychosis (Comprehensive Assessment of At-Risk-Mental-States (CAARMS)^30^), hallucinatory experiences (Specific Psychotic Experiences Questionnaire – Hallucinations subscale (SPEQ-H)^36^), paranoia (Revised- Green *et al* Paranoid Thoughts scale (R-GPTS)^37^) and dissociative experiences (Černis Felt Sense of Anomaly Scale (ČEFSA)^38^) will be assessed.

Levels of depression and anxiety (Depression, Anxiety and Stress Scale (DASS-21)^39^), worry (Dunn Worry Questionnaire (DWQ)^40^), suicidal ideation (Columbia Suicide Severity Rating Scale (C-SSRS)^41^) and self-concept (Brief Core Schema Scale (BCSS)^42^) will be measured.

Social functioning will be assessed using the Work and Social Adjustment Scale (WASA)^43^ and Oxford Agoraphobic Avoidance Scale.^44^ The Process of Recovery Questionnaire (QPR),^45^ EQ-5D-5L (http://www.euroqol.org/) and ReQol^46^ will assess quality of life.

Body mass index (BMI), somatic symptoms (Patient Health Questionnaire 15 (PHQ15)^47^), appearance concerns (Body Esteem Scale for Adults and Adolescents (BESAA)^48^ and substance use (Maudsley Addiction Profile (MAP)^49^) will be measured as markers of physical health. Service use, and other relevant health economic data, will be recorded using the Client Service Receipt Inventory (CSRI).^50^

A qualitative interview will be conducted with a subset of 16 participants (n=10 intervention, n=6 control) after their final assessment. The semi-structured interview will explore participants’ experiences of therapy and trial participation.

### The SleepWell intervention

SleepWell is a psychological intervention designed for young people that targets the key mechanisms which regulate sleep: circadian rhythm, sleep pressure, and hyperarousal.^51–53^

To target circadian rhythm, the timing of sleep, we use light/dark exposure which is the key zeitgeber or time cue for sleep, to re-align sleep patterns with the environment. We also re-establish circadian rhythms using daily activity points.To target sleep pressure, the need for sleep, we increase daytime activity to increase night-time tiredness. We use the motivational benefits of fitness-trackers.To target hyperarousal, which can disrupt sleep despite circadian entrainment and high sleep pressure, the key strategy is stimulus control which enables patients to relearn the association between bed and sleep. We also use worry reduction strategies, cognitive restructuring techniques, and night-time relaxation.

SleepWell has been specifically designed with consideration of the unique aspects of sleep in youth, such as the biological changes in sleep architecture (eg, delayed sleep-phase) and lifestyle factors (eg, exam pressures, increasing independence). For example, SleepWell includes the use of technology-devices, engaging family/friends to support the young person, and adaptations of stimulus control due to environmental constraints such as shared accommodation at university.

The SleepWell intervention is manualised in a modular format. The five core modules include: (1) psychoeducation, assessment and goal setting (eg, actigraphy data are used to monitor sleep patterns and identify foci for change); (2) establishing the environmental and lifestyle context for sleep; (3) stimulus control and strategies to reduce hyperarousal; (4) circadian entrainment (using light/dark exposure, setting the sleep window, boosting zeitgebers, for example, meal and activity times); and (5) relapse prevention. Additional modules are selected by patients on the basis of individual need, enabling the intervention to be personalised to the individual’s needs (eg, night-time worry). The format and manuals have been developed in collaboration with our LEAP.

The intervention is delivered by a clinical psychologist, on an individual basis in up to eight 1-hour sessions. There is typically one session per week. Additional contact between sessions (eg, text messages, email) is provided to support treatment strategy implementation. A treatment dose is defined as four or more sessions. In line with the International Early Psychosis Association recommendations that interventions are provided flexibly and in low stigmatising environments, sessions are held in the patient’s home or local health service clinic.^54^ At the final session, participants will be asked to complete a self-report questionnaire to assess the acceptability of the intervention (AARP^55^).

SleepWell will be provided in addition to usual care. With patient consent, sessions will be audio-recorded and independently rated for quality, including fidelity and competence.

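### The AARP is collected only at the final therapy session, so patients who stop SleepWell without a planned last session give no acceptability score

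*Protocol article*

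**What the plan says.** Objectives section of the protocol article: "The primary objective is to assess the feasibility and acceptability of a targeted sleep intervention to prevent psychosis in young people at ultra-high-risk". Table 1 gives several measures under this primary objective. One entry reads "Location and attendance at treatment sessions; content covered in treatment sessions; feedback from qualitative interviews; treatment acceptability score (AARP"); another reads "Number of patients identified, recruited, declined and retained".

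The timing of the two direct sources of patient opinion is fixed elsewhere:

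- **AARP** (The SleepWell intervention): "At the final session, participants will be asked to complete a self-report questionnaire to assess the acceptability of the intervention".
- **Interviews** (Assessments): "A qualitative interview will be conducted with a subset of 16 participants (n=10 intervention, n=6 control) after their final assessment". The last scheduled assessment is at 9 months (Trial design and flow chart).

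The SleepWell intervention section also says that therapy is given "on an individual basis in up to eight 1-hour sessions", and that "A treatment dose is defined as four or more sessions". It does not define which session counts as final.

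**The concern.** The form is tied to an event that some allocated patients will not reach. Someone who simply stops coming has no final session at which to receive it. The four-session definition of a dose adds to this: a patient can attend four or five sessions, count as treated, stop unplanned and still have no score.

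The missing scores are unlikely to be a random subset. A patient who disliked the therapy, or found it too demanding, is more likely to stop. The observed scores would then come from those best disposed to the treatment. A feasibility trial needs the views of the others as well, because they show what to amend before a definitive trial. No analysis plan can recover ratings that were never collected.

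The interviews have a narrower gap. They depend on the final research assessment and not on completing therapy, so the people out of reach are those who leave the trial before 9 months.

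**Working it through.** **The plan's own figures.** The article states no precision or target for acceptability. The nearest figures are in the Analysis section, for 40 participants. Wilson intervals reproduce both:

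- recruitment 20/40 = 50%: 35.2% to 64.8% (stated 35% to 65%);
- retention 32/40 = 80%: 65.2% to 89.5% (stated 65% to 90%).

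**Inputs for the AARP check**

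- N = 20 patients allocated to SleepWell (Analysis).
- n = number who reach a final session and complete the AARP. Not given; assumed 10, 15 or 18.
- k = number of those who rate the therapy favourably. The article calls the AARP a score and gives no cut-off, so a favourable/unfavourable split is also assumed.

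**Bounds.** Without any assumption about the missing patients' views, the proportion favourable among all N lies between

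- lower bound = k / N (every missing patient unfavourable);
- upper bound = (k + N − n) / N (every missing patient favourable).

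| n completing | k favourable | Observed k/n | Lower k/20 | Upper (k + 20 − n)/20 |
|---|---|---|---|---|
| 18 | 18 | 100% | 18/20 = 90% | 20/20 = 100% |
| 15 | 15 | 100% | 15/20 = 75% | 20/20 = 100% |
| 15 | 12 | 80% | 12/20 = 60% | 17/20 = 85% |
| 10 | 10 | 100% | 10/20 = 50% | 20/20 = 100% |

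The width is (N − n)/N whatever k is: 10 points with 2 missing, 25 points with 5 missing, 50 points with 10 missing.

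**Why 15 of 20 is a reasonable illustration.** The Analysis section counts treatment uptake of 75% or more as meeting the progression criterion, and 0.75 × 20 = 15. The criterion can therefore be met with 5 of 20 not taking up treatment. The article does not equate uptake with reaching a final session, so this link is an assumption. Patients who take up therapy but stop unplanned would add to the missing scores.

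**Interviews.** At the 80% retention used for the sample size, 0.20 × 40 = 8 participants would have no 9-month assessment and, as written, could not be interviewed. Over the stated interval of 65% to 90%, the number is 14 down to 4. If retention is equal by arm (assumed), the 10 intervention interviewees come from about 16 patients.

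**The case against.** **Refusal and drop-out are recorded for everyone.** A reader might infer that acceptability as a whole is measured only in completers. The documents do not support that. Table 1 also counts attendance and the numbers declining and retained. The Analysis section documents treatment receipt and follow-up for all recruited participants, and formal complaints about therapy are logged (Adverse events). This stands, and it limits the point to the rating itself: counts show that people left, not what they thought.

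**Interviews do not exclude therapy drop-outs.** A reader might infer that anyone who found SleepWell unacceptable is shut out of both sources. That is too strong. A patient who stops therapy but stays in follow-up can still be interviewed. Only those who leave both therapy and the trial miss both.

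**Interview timing is defensible.** Interviews cover the trial as well as the therapy, and include six controls. Interviewing people who still face a blinded assessment could put the blind at risk. This stands for everyone who remains in follow-up.

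**A final session may be an agreed early ending.** With a maximum of eight sessions, that is a fair reading, and such patients would be scored. Unplanned stoppers would not.

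**Few may stop.** The case series in the Rationale section reports 89% attendance. That is an attendance rate in 12 uncontrolled patients, not the share reaching a last session, but it makes the smaller losses in the table credible.

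**No progression decision is shown to turn on the AARP.** The criteria named in the Analysis section are recruitment, retention and treatment uptake, all of which count leavers. This stands and lowers the stakes.

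**Detail may sit in the full protocol.** Interview sampling and contact with withdrawals may well be there, so silence on them is not an error. The AARP timing is different: the article states it.

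A reader might also infer that patients are rating their therapist in front of the therapist. The article says the questionnaire concerns the intervention, and does not say who collects it or sees the answers.

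**Conclusion.** The point holds for the AARP. As the article stands, patients who stop therapy without a planned last session give no score on a measure listed under the primary objective, and the reported score is likely to be too favourable. That direction rests on one assumption: that stopping is related to low acceptability. It is plausible but not certain. With 12 of 15 favourable, the range of 60% to 85% extends 5 points above the observed 80% as well as 20 points below it.

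The size of the bias cannot be stated. A single figure would need an AARP cut-off, a completion rate and the difference between completers and stoppers, and the article gives none of them. The 75% to 100% range for 15 of 20 shows what the missing scores could hide; it does not estimate the bias.

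For the interviews, only a modest improvement in who is invited is warranted. The 9-month timing for participants in follow-up should stay.

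**What to change.** 1. **AARP timing.** Offer the AARP to every patient allocated to SleepWell who started therapy, at one fixed time (the planned end of therapy) or on stopping if that is earlier. Send it by post or online, and not through the blinded assessor.
2. **AARP reporting.** Give the number of responses out of all 20 allocated, so that those who never started remain visible in the denominator. Show scores separately for patients with fewer than four sessions.
3. **Interviews.** Keep the total of 16. Reserve some of the 10 intervention places for patients who stopped therapy early, interviewed after the 9-month assessment if they remain in follow-up. Invite those who withdraw from the trial when they leave, since no later blinded assessment is then at risk.

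The cost is a few sentences of procedure and a mailed or online form. The instruments, sample size and number of interviews do not change, and no clinical rule is affected. Some early leavers will not respond, but that non-response can itself be reported. If the full protocol already makes these arrangements, the article's wording on AARP timing should be brought into line with it.
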